### Randomization and blinding

Randomization sequence will be generated by a designated staff not involved in outcome data collection and analysis, who will use the block randomization method via SPSS version 22.0 (International Business Machines Inc., USA), with an electronic table of random numbers to allocate eligible participants to either of the two groups (in a 1:1 ratio). The allocation sequences will be prepared and be kept inside sealed, opaque, and consecutively numbered envelopes. The envelope will be opened by the neurosurgeons in charge, who will then prepare the study solution based on the respective allocation scheme and be therefore made aware of group assignations. Participants will be enrolled by a dedicated research nurse not involved in the data collection and analysis, and the neurosurgeons in charge are responsible for assigning participants to interventions. This is an open-label design with only patients and independent researchers in charge of follow-up and data analysis blinded to allocation. The D-PAL is a lipid emulsion in the infiltration solution, which can be easily distinguished from the clear ropivacaine alone study solution. Therefore, unblinding will not occur.

Prior to the commencement of the study, all investigators will receive standardized training on trial content, treatment strategies, evaluation, and quality control. All interventions will be carried out in accordance with clinical practice guidelines. During preoperative visit, eligible patients should be acquainted with pain NRS ranging from 0 (no pain) to 10 (worst possible pain) [31]. They will be guided on how to use a patient controlled analgesia (PCA) device.

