### Pre-incisional infiltration

Patients will receive pre-emptive infiltration by the neurosurgeon immediately before head fixation in a sterile fashion. A 22-gauge needle will be introduced into the planned incision site, as well as each pin fixation site of the Mayfield head holder, at a 45° angle and throughout the entire thickness of the scalp. The ropivacaine plus D-PAL group will receive 0.027% D-PAL and 0.5% ropivacaine, whereas the ropivacaine alone group will be injected with 0.5% ropivacaine alone. The total volume of the local infiltrated solution will be at the discretion of the neurosurgeon, based on the length of the incision.

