### Outcome measures

#### Baseline data

The demographic characteristics include age, gender, BMI, ASA status, neurological pathology, and comorbidity. Surgery and anesthesia characteristics include surgical site, length of incision, volume of local infiltration solution, duration of surgery and anesthesia, intraoperative analgesics (sufentanil and remifentanil) consumption, perioperative hemodynamic parameters, cumulative intravenous dexamethasone prescribed by a neurosurgeon, etc.

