### Sample size

Earlier studies have reported that incision-site infiltration with ropivacaine plus dexamethasone could reduce about 30-50% of postoperative pain severity compared with ropivacaine alone [6, 19, 22]. Based on these literatures and our clinical experience, we hypothesize that the pain NRS scores was approximately 2.0 ± 1.5 (mean ± standard deviation) scores in the ropivacaine alone group and attempt to detect a difference of 40% in pain NRS scores between groups at 24 h after craniotomy. Therefore, the pain scores would be about 1.2 ± 0.9 scores in D-PAL plus ropivacaine group at 24 h after craniotomy. PASS V.11 software (NCSS, Kaysville, UT, USA) is used for sample size calculation with *α* = 0.05, *β* = 0.1, and power = 90%. Considering a dropout rate of 20%, a total of 130 patients will be required in this trial (*n* = 65 per group).

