## Discussion

In this prospective, randomized controlled trial, we seek to determine whether pre-emptive scalp infiltration with the addition of D-PAL emulsion to ropivacaine would offer superior analgesic efficacy for post-craniotomy pain compared to ropivacaine alone. To the best of our knowledge, this is the first study to evaluate the effects of D-PAL emulsion in scalp infiltration for craniotomy. D-PAL emulsion, dexamethasone palmitate incorporated into lipid microspheres, has a stronger anti-inflammatory activity, as well as a longer duration of action and fewer side effects than free dexamethasone. The clinical utility of D-PAL emulsion has been reported to treat inflammatory diseases or pain diseases by intravenous administration or local infiltration [24, 25, 28, 29, 37]. In this study, we intend to choose the concentration of about 0.027% D-PAL (equivalent to 0.017% dexamethasone) for scalp infiltration, which seems to be the lowest possible concentration of dexamethasone for local use according to previous literatures [6, 37–39]; thus, it should be considered safe and help reduce the potential risks of local glucocorticoid, such as delayed wound healing and wound infection. It is true that systemic dexamethasone has become the standard pharmacological agent in the treatment of cerebral oedema associated with intracranial tumors [40]. Perioperative high-dose of dexamethasone in craniotomy has been reported to be associated with hyperglycemia, infection, peptic ulcer, and decreased incidence of PONV and pain [41]. All these may confound our findings. So the consumption of intravenous dexamethasone prescribed by the neurosurgeon should be calculated in the two groups.

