Craniotomy site may be a determinant for the incidence and intensity of post-craniotomy pain, which is partly explained by the anatomical location of peri-cranial muscles being damaged. Studies suggest that patients undergoing infratentorial procedures may have more pain than those submitted to a supratentorial approach [2]. Further studies indicate that supratentorial craniotomy involving temporal muscle incision is assumed to be more painful, while the procedure involving frontal muscle incision tends to induce the lowest pain [51]. Therefore, we specify the accurate location in this trial and restrict the surgical approach to be supratentorial.

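### The primary comparison leaves out craniotomy site, which the protocol expects to affect pain, and values arising after allocation are filed and tested as baseline

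*Protocol article*

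**What the plan says.** **Site.** The Discussion says craniotomy site may determine how often and how strongly patients have pain. Within supratentorial surgery, "supratentorial craniotomy involving temporal muscle incision is assumed to be more painful", and frontal incision tends to hurt least. The protocol responds by admitting only supratentorial cases and specifying the location. Surgical site is recorded under *Baseline data*.

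**Primary analysis.** The Statistics section compares the 24 h NRS by a two-tailed t test, or by Mann-Whitney U if the data are not normal. No covariate is named. *Randomization and blinding* describes 1:1 block randomisation without stratification.

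**Items called baseline.** *Baseline data* also lists infiltration volume, duration of surgery, intraoperative sufentanil and remifentanil, and "cumulative intravenous dexamethasone prescribed by a neurosurgeon". The Statistics section applies the outcome tests to baseline information as well.

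**Who sets them.** "The envelope will be opened by the neurosurgeons in charge", who then prepare the solution and know the arm. The infiltrated volume "will be at the discretion of the neurosurgeon, based on the length of the incision". On steroids, the Discussion accepts possible confounding and concludes: "So the consumption of intravenous dexamethasone prescribed by the neurosurgeon should be calculated in the two groups".

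**The concern.** Two separate matters are at stake.

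First, the restriction to supratentorial surgery removes the infratentorial contrast but not the temporal/frontal contrast described in the same paragraph. A factor that the authors expect to affect the primary outcome, that is known before surgery and that is already recorded, plays no part in the primary comparison. With about 52 evaluable patients per arm this gives up some precision, and any chance imbalance in site stays in the estimate.

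Second, a variable is baseline only if allocation, or knowledge of it, cannot have changed it. A between-arm difference in infiltration volume or in later intravenous dexamethasone could be a consequence of the arm. Under the present label it would be read as baseline imbalance, and a later analyst could take it for a legitimate covariate.

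**Working it through.** **1. The plan's own sample size.** Inputs from *Sample size*: "approximately 2.0 ± 1.5 (mean ± standard deviation) scores in the ropivacaine alone group"; "the pain scores would be about 1.2 ± 0.9 scores in D-PAL plus ropivacaine group"; two-sided α 0.05; power 90%; dropout 20%.

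- Difference: 2.0 − 1.2 = 0.8.
- Normal approximation: n = (1.5² + 0.9²)(1.960 + 1.282)² / 0.8² = 50.2, so 51 per arm.
- Welch t test with the noncentral t distribution: 52 per arm (power 0.903).
- Dropout: 52 / 0.80 = 65 per arm, total 130. The stated figure reproduces without any covariate.

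**2. What adjustment for site could gain.** The documents give no site effect, site mix or explained variance, so R² is an assumption shown as a range. The average SD is √((1.5² + 0.9²)/2) = 1.237. Adjustment reduces it to 1.237 × √(1 − R²). Power at 52 per arm is Φ(0.8 / (SD × √(2/52)) − 1.960), and the required n is 50.2 × (1 − R²), rounded up.

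| Assumed R² | Power at 52 per arm | n per arm for 90% power |
|---|---|---|
| 0 (as planned) | 0.910 | 51 |
| 0.05 | 0.923 | 48 |
| 0.10 | 0.935 | 46 |
| 0.20 | 0.958 | 41 |

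**3. How large a chance imbalance could be.** Assume 30–50% of patients have temporal muscle involvement. The SD of the between-arm difference in that proportion is √(2p(1 − p)/52), which is 0.090 at p = 0.3 and 0.098 at p = 0.5. The probability of a gap of at least 10 percentage points is then 0.27–0.31, and of at least 15 points 0.10–0.13. With an assumed site effect of 0.5–1.0 NRS points, a gap of 10–15 points moves the observed difference by 0.05 (0.10 × 0.5) to 0.15 (0.15 × 1.0). That is 6–19% of the planned 0.8.

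**4. The baseline list against the order of events.**

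- *Infiltration volume*: the surgeon opens the envelope, prepares the solution and injects a volume of their choosing. This is clearly after allocation.
- *Intraoperative opioids*: remifentanil runs to the end of surgery, so it continues after infiltration. Sufentanil is given at induction, and the protocol does not say whether the envelope is opened before or after that. The limitations in the Discussion state that anaesthesiologists are unblinded too.
- *Duration of surgery*: also known only after allocation.
- *Cumulative intravenous dexamethasone*: no start of the count is given. Doses before the envelope is opened are true baseline; later doses are prescribed by a surgeon who knows the arm.

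Surgical site, by contrast, can be fixed from the operative plan before the envelope is opened.

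**The case against.** The strongest reply is that nothing in the primary analysis is wrong. Under 1:1 randomisation the unadjusted comparison is valid, and N = 130 meets its stated power. A reader might infer that leaving out site biases the result or makes the trial too small; the documents support neither. At R² = 0.05 the gain is only from 0.910 to 0.923. The authors also did not overlook site: they restricted the approach, record the location, and word its role cautiously. All of this stands and limits the point to precision and chance imbalance. Age and sex are not named as drivers of pain, so there is no ground here to require them in the model.

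A reader might also infer that the surgeon's steroid prescribing will differ by arm and bias the result. The documents do not show this. Volume is tied to incision length, and the Discussion gives systemic dexamethasone a clinical use in tumour-related oedema. Setting intravenous milligrams against the 5 mg dexamethasone equivalent in the full solution (2 mL × 2.5 mg/mL) shows little, because the Background claims quite different uptake and activity for D-PAL. Adjusting for intended steroid use would not remove differential prescribing after allocation either. Tabulating later doses by arm, as the Discussion proposes, is the right handling of those values; the fault lies in the baseline label and the testing.

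Nor does the protocol plan any adjustment for post-allocation values. That remains a risk created by the label.

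Finally, linear regression on a bounded, probably skewed score may draw objection. With about 52 per arm, a difference in means with robust standard errors is reasonable, and it is the quantity on which the trial was sized. The rank test can stay as a check.

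**Conclusion.** The point holds as an improvement to the primary analysis and a correction to the variable list. The unadjusted test is valid and the total of 130 stands.

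Adjusting for site would raise power at 52 per arm from 0.91 to 0.92–0.96, if site explains 5–20% of the variance in 24 h NRS. That range is assumed, as are the site mix and site effect behind the imbalance figures.

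The second part needs no assumption about size. Infiltration volume, opioid use during surgery and any dexamethasone given after allocation are not baseline and should not be tested as such. How much of the dexamethasone count precedes allocation cannot be told from the document.

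**What to change.** 1. Prespecify the primary analysis as a linear regression (ANCOVA) of 24 h NRS on arm and planned surgical site (temporal muscle involved or not), recorded before the envelope is opened. Use robust standard errors, because the plan assumes unequal SDs. Keep the t test or Mann-Whitney U test as a sensitivity analysis.
2. Steroid use before allocation may be added as a covariate if it is recorded.
3. Move infiltration volume, intraoperative opioid use and intravenous dexamethasone given after allocation out of *Baseline data* into a list of post-randomisation perioperative variables. Report them by arm, without baseline balance tests, and do not use them as covariates.
4. Record dexamethasone doses before and after allocation separately.

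The cost is slightly more analysis work and a few added case report form entries (planned site, and dexamethasone split by timing). N does not change. The *Trial status* section says recruitment had not begun, so on that text the change could be made before any data exist.

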## Trial status

Not recruiting. Protocol (V3.2/2018-07-05). The recruitment will be expected to begin on October 1, 2022, and to be completed on May 1, 2023.

## Data Availability

The datasets which will be used and/or analyzed during this study are available from the corresponding author on reasonable request.

## Abbreviations

D-PAL: Dexamethasone palmitate emulsion
PCA: Patient-controlled analgesia
NRS: Numerical rating scale
OC/APAP: Oxycodone /acetaminophen
Dex: Dexamethasone
PONV: Postoperative nausea and vomiting
WHOQOL-BREF: World Health Organization QoL abbreviated version
POSAS: Patient and Observer Scar Assessment Scale
BP: Blood pressure
HR: Heart rate
SpO_2_: Pulse oxygen saturation
BIS: Bispectral index
NSAIDs: Nonsteroidal anti-inflammatory drugs
